### Statistical analysis

The analyses will be described in detail in a full Statistical Analysis Plan. In brief, each intervention is hypothesised to be superior to SOC and, therefore, the proposed analysis is intention-to-treat, including all randomised patients. The primary analysis will compare: a) transfusion versus no transfusion (strata b only) and b) 20 ml/kg versus 30 ml/kg (strata a and b) in terms of the proportion of children with fatal outcome 28 days after randomisation. Primary outcome analysis will use time-to-event methods (Kaplan-Meier, log-rank test, proportional hazards models) to the timepoints specified for primary and secondary outcomes, stratified by centre and anaemia severity at baseline. Correction of anaemia will also be analysed using time-to-event methods.

Pre-specified subgroup analyses will include each of the other randomised allocations (ie exploration of interactions in the factorial design), together with the other randomisation stratification factor (centre) and the anaemia stratification factor (a versus b) for the transfusion randomisation. We will also investigate a priori whether there was any evidence for a different impact of the interventions according to the following categorical variables: previous receipt of a transfusion (ever or at another health centre in this illness); speed (rate) at which the transfusion is administered; fever; malaria; microbiological evidence of sepsis (blood culture or retrospective molecular diagnosis); HIV; known or previously undiagnosed sickle cell disease.

For the cotrimoxazole prophylaxis and MVMM supplementation randomisations the primary analysis will be intention-to-treat based on all randomised participants, as above. However, secondary analyses will be restricted to: (i) patients discharged alive, and (ii) patients discharged alive in whom these interventions were neither mandated nor contraindicated (ie excluding HIV-infected children and those with known GP6D deficiency from the cotrimoxazole randomisation, and excluding children admitted for severe acute malnutrition from the supplementation randomisation).

Secondary outcome measures will be analysed using time-to-event methods or normal linear regression for continuous variables. The frequency of hospital re-admissions and adverse events will be tabulated by body systems and by randomised groups, and the number of events experienced by each participant will be compared across randomised groups using Fisher’s exact test.

For the within-trial cost-effectiveness analysis, the differential cost of the treatment interventions will be related to their differential outcomes in terms of the primary outcome. The relative cost-effectiveness of the alternative forms of management will then be assessed using standard decision rules and a full stochastic analysis will be undertaken. A cost-utility analysis will also be conducted using a standard approach. The within-trial analysis will be augmented by extrapolation beyond the trial follow-up using decision-analytic modelling. The aim of this analysis will be to predict the implications of any difference in clinical endpoints in the trial for subsequent quality-adjusted survival duration and long-term resource costs. This will inform the question of whether any differences in drug costs between the treatment groups are offset by reduction in other treatment costs or health improvements in the long term.

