### Current WHO recommendations

#### Transfusion

To avert overuse of blood products the WHO advocates a conservative transfusion policy, reserving blood for children with a haemoglobin (Hb) < 4 g/dl (or < 6 g/dl if accompanied by complications). Although not systematically evaluated, this conservative transfusion policy has been incorporated in WHO paediatric hospital practice guidelines. However, the specific recommendations in these guidelines contain inconsistencies and ambiguities [9] resulting in variation in practice across African countries, most particularly in the subgroup with ‘uncomplicated’ SA (Hb 4–6 g/dl without severe symptoms) where transfusion avoidance is recommended [4, 8]. A Cochrane review including the only 2 African randomised controlled trials (RCTs) [10, 11] conducted to date (involving 114 and 116 children randomised to blood transfusion or oral haematinics) concluded that there was insufficient information on whether routinely giving blood to clinically stable children with SA either reduces death or results in a higher haematocrit measured at 1 month, and indicated the need for a definitive trial [8].

Overall mortality in children with Hb < 4 g/dl or SA with life-threatening complications is 15 % [5]. Clinical studies in Kenya [12, 13] have shown that profound anaemia (Hb < 4 g/dl) is independently associated with death (odds ratio; OR = 2 · 5), as is SA (defined in this study as a Hb < 5 g/dl) complicated by reduced consciousness (OR = 7 · 4) or respiratory distress (OR = 4 · 1). Many deaths occur within 48 hours of admission, with 25–50 % [14, 15] occurring within 6 hours. In the FEAST trial, which enrolled children with shock, a higher case fatality was found in those with anaemia compared to those without anaemia, irrespective of intervention group [16]. In children with uncomplicated SA – Hb 4–6 g/dl without prostration or respiratory distress – overall case fatality is 4–6 %, being lower in parasitaemic children (2–3 %) [17] than in those with negative malarial slides (8–10 %) [12]. The ratio of complicated to uncomplicated SA is commonly 1:1 [18].

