### Trial treatments

#### Randomisation procedures

Randomisation in each part of the factorial will be stratified by centre and the other randomisations in the factorial. Randomisation lists, using variable block sizes, will be generated and kept at the Medical Research Council Clinical Trials Unit (MRC CTU), London. The randomisation envelopes and clinical packs will be prepared before the trial, with 1 set for complicated SA (R1a) and 1 for uncomplicated SA (R1b). Eligible children will be screened and recruited at the time of hospital admission. At enrolment sealed consecutively numbered opaque envelopes (opened in strict numeric order) will assign a TRACT trial number and indicate a clinical pack number. The clinical pack will be within the first 10 packs in the study filing cabinet but will not necessarily be the first remaining clinical pack number (an additional level of allocation concealment). Once opened, the clinical pack contains case report forms (CRFs) and a card which confirms the TRACT trial number, and simultaneously assigns transfusion interventions R1a/b (according to SA strata), micronutrient support (R2) and antimicrobial prophylaxis (R3) randomly. A similar system has worked well in the emergency care trial, FEAST [16].

The randomisation procedures and adherence to allocated treatments are reviewed at each independent monitoring visit. The process for this is detailed within the monitoring Standard Operating Procedure (SOP). The monitors are requested to check at each participating site whether: a) the randomisation envelopes are being correctly stored and used; b) whether enrolled children are allocated to the correct arm and c) that the allocated trial treatments (transfusion, MVMM/iron or folate and cotrimoxazole) were received by the child. It is also monitored electronically through central database monitoring, and also that both the Data Monitoring Committee (DMC) and the Trial Steering Committee (TSC) will monitor overall adherence to each of the randomised allocations.

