#### R1 transfusion strategies

At enrolment children will be assessed at admission and will be divided into 2 groups for randomisation (R1a and R1b: see Table 2) based on: i) haemoglobin level, and ii) assessment of clinical severity children or complications (reduced conscious level; respiratory distress, acute history of haemoglobinuria or an established diagnosis of sickle cell disease).

**Table 2 Tab2:** Transfusion sub-groups

R1a Complicated severe anaemia: Hb < 4 g/dl *or* a Hb < 6 g/dl *plus* 1 or more signs of severity or complications
R1b Uncomplicated severe anaemia: Hb ≥ 4 and < 6 g/dl without any of the severity features or complications

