### Sample size calculation and statistical analysis

#### Sample size

The sample size calculation is based on the following assumptions:80 % power, 2-sided alpha = 0.013 to allow for 4 comparisons (see below)SA cases are 50 % complicated (< 4 g/dl or 4–6 g/dl with prostration/respiratory distress/known sickle cell disease/haemoglobinuria) and 50 % uncomplicated (4–6 g/dl without prostration, respiratory distress, known sickle cell disease or haemoglobinuria) [12] (and [name] personal communication)Mortality (cumulative) at 48 hours and 4 weeks is 11 % and 16 % respectively in complicated SA, and 4 % and 9 % in uncomplicated SAThe cumulative rate of re-admission, SA relapse and re-transfusion at 6 months is 12.5 % in both complicated and uncomplicated SA (in addition to mortality above)For the primary comparison of transfusion versus no transfusion in uncomplicated SA at 4 weeks, the minimum clinically relevant difference is a 50 % relative reduction (R1b): for the other primary comparison of transfusion volume (20 versus 30 ml/kg) at 4 weeks (R1a and 1b), the minimum clinically relevant difference is a 30 % relative reduction. The minimum clinically relevant difference is larger for the transfusion versus no transfusion question as provision of safe blood at all will require greater resources than provision of slightly larger versus slightly smaller blood volumes. As the same relative difference translates to a far larger absolute difference at higher event rates, for the primary comparison at 6 months (R2/3) the minimum clinically relevant difference is a 5 % absolute reduction (see below for control group event rates). Then:(R1b) comparison of transfusion versus no transfusion (50 % reduction from 9 % control mortality at 4 weeks) requires 1460 uncomplicated SA cases (1:1 allocation to 30/20 ml/kg:no transfusion, 730 in no transfusion group, 365 receiving 20 ml/kg and 365 receiving 30 ml/kg transfusions)(R1a and 1b) if the overall ratio of uncomplicated:complicated SAs is 1:1 (ie 50 % of each type), then within the subgroup randomised 1:1 to 30 versus 20 ml/kg, the ratio will be 1:2 because this comparison excludes the 50 % of uncomplicated SA randomised to no transfusion. Overall mortality at 4 weeks in this group will, therefore, be 13.67 % (0.33 × 9 % + 0.67 × 16 %). The comparison of 30 versus 20 ml/kg (30 % reduction, to 9.57 %) requires 2798 SAs, 1399 per group (split 466 uncomplicated, 933 complicated)Therefore, comparing required sample sizes for R1a and R1b, to address both parts of the transfusion question (R1) we need slightly more uncomplicated SA children per group from (R1a and 1b – *n* = 466) than (R1b – *n* = 365), and therefore the total sample size is 3730 cases (933 × 2 = 1866 complicated, 466 × 4 = 1864 uncomplicated)(R2/3) the comparison of multi-vitamins versus SOC (1:1) and cotrimoxazole prophylaxis versus SOC (1:1) requires 3162 SA cases, assuming 50 % are complicated and 50 % uncomplicated, to detect a 5 % absolute reduction from average control mortality of 25 % (0.5 × 21.5 % + 0.5 × 28.5 % at 4 weeks).

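### The stated primary mortality analysis leaves prognostic variation within the complicated stratum unused and may forgo roughly 0 to 7 points of power for 20 versus 30 ml/kg

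*Protocol article*

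**What the plan says.** - **Analysis.** The Statistical analysis section of the protocol article specifies Kaplan-Meier, log-rank and proportional hazards methods for the primary outcome, "stratified by centre and anaemia severity at baseline". It names no further covariate for the primary model and refers to a full SAP for detail.
- **Severity factor.** R1 transfusion strategies and Table 2 divide children into two strata. Haemoglobin below 4 g/dl alone places a child in R1a. So does haemoglobin below 6 g/dl with any one of these: "reduced conscious level; respiratory distress, acute history of haemoglobinuria or an established diagnosis of sickle cell disease". R1b holds children at 4 to 6 g/dl with none of them.
- **Prognosis.** The Background section on transfusion gives an odds ratio for death of 2.5 for haemoglobin below 4 g/dl. It also gives odds ratios for severe anaemia "complicated by reduced consciousness (OR = 7 · 4) or respiratory distress (OR = 4 · 1"), with severe anaemia defined in that source as haemoglobin below 5 g/dl.
- **Randomisation.** "Randomisation in each part of the factorial will be stratified by centre and the other randomisations in the factorial".
- **Planning figures.** The Sample size section sets "80 % power, 2-sided alpha = 0.013 to allow for 4 comparisons". It takes control mortality as 16% in complicated and 9% in uncomplicated children, which pools to 13.67% when complicated children make up two thirds. On the number needed it states: "The comparison of 30 versus 20 ml/kg (30 % reduction, to 9.57 %) requires 2798 SAs, 1399 per group".

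**The concern.** Stratum R1a mixes children at very different risk. An alert child with haemoglobin of 3.9 g/dl sits in the same stratum as an unconscious child in respiratory distress. If the cited odds ratios are even roughly right, much of the predictable variation in 28-day death lies inside this stratum, and a two-level factor cannot use it.

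In a proportional hazards model, leaving out strong baseline predictors pulls the estimated hazard ratio towards 1 and costs power. Here the predictors are assessed at enrolment to allocate the stratum, so they precede treatment and need no new data collection.

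The comparison most exposed is 20 versus 30 ml/kg. It has the smallest absolute target difference in the plan: 4.1 points (13.67% to 9.57%), against 4.5 points for transfusion versus none (9% to 4.5%) and 5 points for R2 and R3. The Discussion describes blood supply as a constraint on enrolment, so extra precision from recruitment would be hard to obtain.

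A smaller mismatch is that randomisation is stratified by the other factorial allocations, while the stated primary analysis is not.

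**Working it through.** **1. Reproduce the plan's figure.** Inputs from the Sample size section: p1 = 0.1367, p2 = 0.0957, two-sided alpha 0.013 (z = 2.484), power 80% (z = 0.842). Let d = p1 − p2 = 0.041 and let p̄ be the mean of p1 and p2.

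n0 = [2.484·√(2p̄(1−p̄)) + 0.842·√(p1(1−p1) + p2(1−p2))]² / d² = 1349.8 per group.

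With continuity correction: n = (n0/4)·[1 + √(1 + 4/(n0·d))]² = 1398.1, rounded up to 1399, so 2798 in total. This matches the plan exactly. The same formula gives the stated 1460 (R1b) and 3162 (R2/R3).

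**2. Power of the analysis as planned, at 1399 per group.**
- Two proportions without continuity correction: 81.6%.
- Log-rank: hazard ratio = ln(1−0.0957)/ln(1−0.1367) = 0.684; deaths = 1399 × (0.1367 + 0.0957) = 325; power = Φ(|ln 0.684|·√(325/4) − 2.484) = 82.5%.

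The planned analysis therefore has about 82% power.

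**3. Do the odds ratios fit the planning rates?** At 9% mortality without any feature, the odds are 0.09/0.91 = 0.0989. Applying only the weakest odds ratio, 2.5, gives odds of 0.247, a risk of 19.8%. That already exceeds the 16% planned for all complicated children. The other two give 28.9% (4.1) and 42.3% (7.4). The full odds ratios and the two planning rates cannot all hold together, so the gain has to be shown under several readings.

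**4. Simulated gain.** 932 uncomplicated and 1866 complicated children; complicated control mortality held at 16%; overall 30% risk reduction; alpha 0.013; 1500 trials per scenario. The stratified Cox model was compared with the same model plus the three features. Assumed prevalences in complicated children are listed as reduced consciousness / respiratory distress / haemoglobin below 4 g/dl. An asterisk marks mixes in which 15% have none of the three.

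| Reading of the odds ratios | Prevalences (%) | Planned | Adjusted | Gain (points) |
|---|---|---|---|---|
| Full | 3/10/50 | 81.8 | 85.3 | 3.5 |
| Full | 5/20/50 | 80.3 | 85.3 | 5.0 |
| Full | 20/40/50 | 83.0 | 89.7 | 6.7 |
| Full | 10/20/50* | 80.5 | 84.6 | 4.1 |
| Full | 20/40/50* | 80.9 | 88.0 | 7.1 |
| Full on 48-hour deaths (11%), then 5 points more to 4 weeks for all | 10/20/50* | 82.2 | 84.9 | 2.7 |
| Same | 20/40/50* | 82.3 | 86.0 | 3.7 |
| Log odds ratios halved | 10/20/50 | 79.9 | 81.2 | 1.3 |
| Same | 20/40/50 | 81.8 | 83.8 | 2.0 |
| Same | 30/50/60 | 81.7 | 84.0 | 2.3 |
| Scaled so 9% and 16% both hold | 10/20/50* | 81.3 | 81.7 | 0.5 |
| Same | 20/40/50* | 83.7 | 83.9 | 0.1 |

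Gains were taken before rounding. Monte Carlo error is about 1 point on each power. With no treatment effect, rejection was 0.013 (planned) and 0.012 (adjusted), so adjustment does not inflate type I error.

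**5. Other factorial allocations.** These explain about 0.4% of variation; power moves from 80.0% to 80.2%.

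**6. What the gain is worth.** Moving from 82% to 85–87% power corresponds to an information ratio of [(2.484 + z of new power)/(2.484 + 0.915)]², that is 1.07 to 1.13, or about 200 to 360 more children on 2798.

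**The case against.** The strongest reply is that nothing here is an error. The analysis is valid, respects centre and the R1a/R1b split, and meets its 80% power. The article gives a brief account and leaves detail to an SAP that is not shown, where covariates would often appear. The size of the gain also rests on prevalences the article does not give. The odds ratios come from other studies, are defined at haemoglobin below 5 g/dl for the two signs, and are not shown to be mutually adjusted within R1a for 28-day death. Calibrated to 16%, the full odds ratios can put children whose only feature is haemoglobin below 4 g/dl below the 9% planned for uncomplicated children.

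All of that stands as a limit on the size and seriousness of the point. It does not remove it: the article states a concrete primary analysis, and its own Background gives the reason a better one is available.

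Several stronger readings are tempting and are not supported:
- *That the plan ignores these features.* The two-level stratum is built from them. Only variation inside R1a goes unused.
- *That adjustment is restricted to these two factors.* The text names no others but does not exclude them.
- *That a fixed loss of about 5 points follows from the documents.* It needs the full odds ratios and assumed prevalences.
- *That the signs cannot be missing.* Haemoglobin below 4 g/dl alone assigns R1a, so stratum assignment does not guarantee that each sign was recorded.
- *That this comparison has the smallest relative effect.* R2 and R3 target 25% to 20%, a 20% relative reduction, against 30% here.

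**Conclusion.** The point holds as a missed efficiency. The stated primary analysis uses the severity features only through a two-level factor, and two thirds of the 20 versus 30 ml/kg comparison (933 of 1399 per group) lie in the stratum where they still vary. Against about 82% planned power, the analysis may forgo roughly 0 to 7 points: about 3 to 6 if the cited odds ratios carry over, and near 0 to 2 if they are scaled down towards the 9% and 16% planning rates. The spread reflects the conflict between the odds ratios and those rates, and the unknown prevalences; the documents cannot narrow it. Leaving out the other factorial allocations has a negligible effect on power and matters only for agreement between design and analysis. No gain was calculated for transfusion versus none in R1b, where the signs are absent by definition, or for R2 and R3.

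**What to change.** Keep stratification by centre and severity. Before database lock, pre-specify that the primary hazard ratio and p-value come from a proportional hazards model that also includes baseline haemoglobin, reduced consciousness (yes/no), respiratory distress (yes/no) and indicators for the other factorial allocations. State how any missing sign is handled. Report the analysis without these covariates, with the Kaplan-Meier curves, as supportive. If the full SAP already does this, no change is needed beyond making the two documents agree.

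The cost is a sentence or two and no new data. The hazard ratio becomes conditional on the covariates, and the primary p-value no longer comes from the simple stratified log-rank test.

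### The primary log-rank and Cox analyses leave out the other factorial allocations on which the randomisation was stratified; the test stays valid, and adding them is a small, free improvement

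*Protocol article*

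**What the plan says.** On allocation, Randomisation procedures states: "Randomisation in each part of the factorial will be stratified by centre and the other randomisations in the factorial". Packs are prepared "with 1 set for complicated SA (R1a) and 1 for uncomplicated SA (R1b"), and one card assigns R1, R2 and R3 together. Balance is therefore built in on centre, on severity and across the factorial arms.

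On analysis, Statistical analysis states: "Primary outcome analysis will use time-to-event methods (Kaplan-Meier, log-rank test, proportional hazards models"), run to the specified timepoints and "stratified by centre and anaemia severity at baseline". The other allocations come in the next paragraph, in a different role: "Pre-specified subgroup analyses will include each of the other randomised allocations (ie exploration of interactions in the factorial design"). The section is a summary: "The analyses will be described in detail in a full Statistical Analysis Plan".

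**The concern.** The usual principle is that the primary analysis conditions on the factors used to balance the allocation. Here the article gives a specific list of analysis strata, and it is shorter than the list of factors used in randomising. Pre-specifying interaction analyses by the other allocations does not fill the gap, because an interaction analysis puts nothing into the primary model.

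The trial hopes that the omitted factors affect outcome. If they do, and allocation is balanced across them, a test that leaves them out uses a variance slightly larger than the true one. The Cox hazard ratio is then also an average over the other interventions and sits slightly nearer to 1. At stake is a little precision, and a choice between two defensible hazard ratios that is better settled before results are seen.

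**Working it through.** **1. The plan's own figures.** Inputs from Sample size: "80 % power, 2-sided alpha = 0.013 to allow for 4 comparisons", so z = 2.484 for alpha and 0.842 for power. The three planned contrasts are R1b ("50 % reduction from 9 % control mortality at 4 weeks", i.e. 9 % to 4.5 %), R1a and R1b together (13.67 % to 9.57 %), and R2/R3 (25 % to 20 %). The two-proportion formula with continuity correction gives 730, 1399 and 1581 per group, or 1460, 2798 and 3162 in total. All match the article. None of these sizes depends on the analysis strata.

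**2. Variance left in by omitting one balanced factor.** Take a 1:1 factor with event rates pA and pB, and let p be their mean.

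- Total variance: T = p(1 − p)
- Within-level variance: W = [pA(1 − pA) + pB(1 − pB)] / 2
- r = √(W/T)

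The test that omits the factor uses T, while the true variance is W. Its actual alpha is 2[1 − Φ(2.484/r)]. Its power is Φ(0.842/r), against Φ(3.325/r − 2.484) with the factor in the strata, where 3.325 = 2.484 + 0.842 before rounding.

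| Effect of the omitted factor | T | W | W/T | Actual alpha | Power, omitted | Power, included |
|---|---|---|---|---|---|---|
| 25 % v 20 % | 0.17438 | 0.17375 | 0.9964 | 0.0128 | 80.0 % | 80.2 % |
| 13.67 % v 9.57 % | 0.10270 | 0.10228 | 0.9959 | 0.0128 | 80.0 % | 80.2 % |
| 9 % v 4.5 % | 0.06294 | 0.06244 | 0.9920 | 0.0126 | 80.1 % | 80.4 % |

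Before rounding, the differences in power are 0.12, 0.14 and 0.28 points. The test's standard error is too wide by a factor 1/r, that is by 0.2 % to 0.4 %. With R1 and R3 both omitted from an R2 analysis, they explain 0.65 % to 0.95 % of the outcome variance within severity strata. That is 0.3 % to 0.5 % on the standard error.

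**3. Hazard ratio.** Take R3 at its planned effect, hazard ratio ln 0.80 / ln 0.75 = 0.7757, with one omitted factor of the same size.

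- R3 control: mean survival (0.75 + 0.80)/2 = 0.775, cumulative hazard 0.2549.
- R3 treated: mean survival (0.80 + 0.8411)/2 = 0.8205, cumulative hazard 0.1978.
- Ratio: 0.1978/0.2549 = 0.7760, against 0.7757 conditionally.

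**4. Simulated stratified log-rank tests: centre and severity only, then with the other allocations added.**

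| Setting | Without | With |
|---|---|---|
| R3 power, 3000 runs | 71.7 % | 72.0 % |
| R3 power, two further settings | 72.3 %; 83.5 % | 73.1 %; 83.8 % |
| R2 power, composite, 4000 runs | 74.75 % | 74.93 % |
| R2 power, deaths, 4000 runs | 69.98 % | 69.83 % |
| R3 null rejection, 6000 runs | 0.0150 | 0.0148 |
| R3 null rejection, further run | 0.0123 | 0.0133 |

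The change in power runs from −0.15 to +0.8 points. Monte Carlo error is about 0.8 points on a power from 3000 runs and about 0.0015 on a null rate from 6000 runs. The first and fifth rows assume four equal centres, half of cases complicated, R1 reduced to two levels with hazard ratio 0.80, R2 hazard ratio 0.776 and exponential event times. Only the contrast between columns matters: power is below 80 % where the other effects lower the event rate.

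**5. Which comparisons are touched.** Both R2 and R3 are prescribed from discharge, or day 5 if the child is still in hospital. On the planning rates, 11 of the 16 points of 4-week mortality in complicated anaemia, and 4 of 9 in uncomplicated, fall within 48 hours. R2 and R3 can therefore explain little of the 28-day outcome. R1 can act on the whole 180-day outcome.

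**6. Events available for strata.** R1b has 466 × 4 = 1864 children, 932 transfused and 932 not. Expected deaths are 932 × 0.09 + 932 × 0.045 = 83.9 + 41.9, about 126. Over 4 centres × 2 × 2 = 16 strata that is about 8 each. For R2 or R3, full stratification gives at most 4 × 5 × 2 = 40 strata. Planned 4-week mortality alone, (16 % + 9 %)/2 = 12.5 % of 3730, is about 466 deaths before any treatment effect.

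**The case against.** The strongest reply is that allocation is joint. One card assigns all three treatments within centre and severity, so the only strata that exist before allocation are those two, and both are in the analysis. On this view, stratifying by the other randomisations merely describes how the arms are balanced against each other. A marginal comparison is a standard factorial analysis, and a hazard ratio averaged over the other arms is what it is meant to estimate. The article also defers detail to a Statistical Analysis Plan that is not shown, and nothing in it forbids adjustment.

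Most of this stands. A reader might infer that the analysis disregards its own randomisation, that the factorial estimates are biased, or that worthwhile power is lost. The documents support none of these: the likely prognostic baseline factors are retained, the other arms are balanced by design, and the other allocations are examined as interactions. Nor is the remedy a cell-by-cell analysis; it stays at the margins.

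What the reply does not remove is that the article names a particular set of strata for the primary analysis, and that set is shorter than the one it gives for randomisation. The point rests on that stated rule and not on missing detail. The unseen plan may already settle it.

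**Conclusion.** The point holds as an optional improvement. The planned test is valid and, if anything, very slightly conservative: actual alpha is about 0.0126 to 0.0128 by formula, and the simulated null rates are consistent with 0.013. The gain from including the other allocations is under 1 power point at the planned effects, and one simulated setting showed none. The shift in the hazard ratio is in the fourth decimal place when one factor of the planned R2/R3 size is omitted. The effect falls mainly on R2 and R3 at 180 days and hardly at all on R1 at 28 days.

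These sizes assume the plan's own effects and no important interaction, as the article expects; the gain would grow if a transfusion effect proved larger than planned. The variance formula treats the outcome as binary and one factor as omitted at a time. The 25 % planning rate for R2/R3 includes re-admission, relapse and re-transfusion as well as death, but the conclusion is the same in the simulation restricted to deaths. No trial conclusion is threatened.

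**What to change.** In Statistical analysis, extend the clause on strata along these lines: *each primary analysis is a comparison at the margins, stratified by centre and anaemia severity, and also stratified by or adjusted for the other randomised allocations (R2 and R3 for the R1 comparisons; R1 and the other post-discharge randomisation for R2 and R3)*. For R1b, enter R2 and R3 as covariates instead of adding strata, since about 8 deaths per stratum is thin and smaller centres would have fewer. For R2 and R3 either route is workable.

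The cost is one clause, settled before results by allocation are seen. Sample size, data collection and the interaction analyses are unchanged. If the full Statistical Analysis Plan already says this, nothing further is needed beyond making the two texts agree.
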